#### Data Management

FHCSD has implemented a HIPAA-compliant electronic health record system. This system has built-in access controls, such as passwords and PIN numbers, limited access to protected information, encrypted storage, and an audit trail, which tracks records accessed and by whom. Medical information (eg, HIV status, toxicology results, and medical history) gathered by the FHCSD care coordinators at each in-person visit is deidentified so that investigators at UCSD’s HNRP and AVRC cannot link the unique study IDs to identifying information, such as names or medical record numbers. Participants’ actual names, medical record numbers, and other identifying information remain with the FHCSD at all times.

Participant self-report psychosocial assessments are completed at the FHCSD. To promote data quality, care coordinators continuously assess for unusual patterns of responding (eg, providing the same response to all questions) and missing questions at each study visit. Physical copies of the self-report psychosocial assessments are regularly transferred to the HNRP in a secured case by at least two study personnel. Prior to data entry, questionnaires are double-scored and flagged for missing responses using the code “999.” Assessments are then entered into the secure HNRP database using the participant’s deidentified study ID.

### Outcomes

The primary outcomes of the intervention are undetectable plasma viral load and self-reported ART adherence, as measured by participants’ responses to daily SMS text messages. We hypothesize that a greater proportion of iTAB participants will be virologically suppressed (viral load <40 copies/mL) at the end of the study period (either week 24 or 48) compared to the proportion at study entry. Currently, 77% of African Americans living with HIV receiving services at the FHCSD are virally suppressed. We hypothesize an increase of 11% (ie, from 77% to 88%) in the proportion of participants with undetectable viral loads at study completion. We additionally hypothesize that the rates of viral load suppression after the intervention will be comparable to the general FHCSD non-African American population who did not complete the iTAB intervention. Lastly, we hypothesize high engagement with the iTAB system reflected by high response rates to iTAB SMS text messages and positive feedback regarding the acceptability, satisfaction with, and efficacy of iTAB.

In addition to these primary anticipated results, we hypothesize that participants involved in the iTAB intervention will utilize more comprehensive FHCSD services, have fewer missed appointments, and greater use of substance use and mental health services compared to those not in iTAB.

### Statistical Methods

We will characterize HIV disease characteristics (eg, CD4 count) and psychosocial characteristics of the study population using descriptive statistics. Linear regressions will be used to examine psychosocial factors associated with ART adherence. The number and proportion of virologically suppressed participants at baseline and at the final study visit will be compared. We will use McNemar test for paired proportions to compare virologic control within-subjects using data from the baseline and final study visits. Based on a 2-sided, 1-sample test for proportions to compare the viral suppression rate before and after the 48-week study, we have 74% power to detect an increase of 11% in suppression rate (ie, from the reference 77% to 88%) with N=88 participants and alpha =.05.

In secondary/sensitivity analyses, multivariable conditional logistic regression analysis will be performed to study the association between demographic factors and plasma viral load, adjusting for baseline demographic variables and clinical characteristics. Variables with some association to plasma viral load (*P*<.10) will be included as covariates. Data from participants will also be analyzed using methods appropriate for examining longitudinal data, for instance, linear mixed-effect modeling/multilevel modeling, latent growth curve modeling, and growth mixture modeling. These model types will allow for interpreting fixed effects (average group trajectory), random effects (individual variability), and heterogeneity in shape of longitudinal change. All tests of significance for secondary outcomes will be 2-sided; following standard conventions, a *P*-value of less than .05 will be considered as statistically significant. Appropriate nonparametric alternatives will be considered, if parametric assumptions are not appropriate for the data.

The secondary outcomes of the intervention will be responses from the various Likert-type assessments administered at each study visit (eg, medical mistrust, provider satisfaction, barriers to health care access, and alcohol or illicit substance use) and the iTAB feedback questionnaire. We will use regression-based models to examine the associations between these nonadherence risk factors and other study outcomes (eg, association between perceived efficacy of iTAB and virologic suppression).

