Our research team from the University of California, San Diego (UCSD) HIV Neurobehavioral Research Program (HNRP) and Antiviral Research Center (AVRC) has partnered with one of the top 10 largest (based on the number of patients served) federally qualified health centers, the Family Health Centers of San Diego (FHCSD), to meet the unique sociocultural needs of African American PWH in San Diego by adapting the iTAB intervention. FHCSD is the largest comprehensive HIV/AIDS services provider in the San Diego region, and 11.3% of its patient population are African American. When this project was conceived in 2016, only 77% of African Americans receiving care at FHCSD were virologically suppressed as compared to 90% of the non-African American clinic population. Given this significant disparity, we aimed to implement a culturally tailored bidirectional SMS text messaging intervention to improve ART adherence and related HIV disease outcomes among African Americans receiving care at FHCSD.

This study is a longitudinal project (Individual Community Care for HIV/AIDS Now: Getting Engaged—iC-CHANGE) funded by the California HIV Research Program (CHRP: HD15-SD-059). The formative phase of our intervention study assessed supports and barriers to ART adherence and solicited opinions among a sample of African American FHCSD patients and their providers of HIV care on how to best tailor the iTAB intervention. Suggestions for modification of the iTAB SMS text messaging system included: (1) matching the degree to which SMS text messages disclose HIV-related content depending on participants’ level of comfort; (2) variability of SMS text messages, incorporating positive, inspirational, entertaining, and culturally tailored content to their health; (3) personalization of SMS text message content and timing of SMS text messages; (4) positively reinforcing SMS text messages to encourage future adherence; and (5) tracking adherence over time using calendars to facilitate conversations between patients and care coordinators [26]. We also included culturally relevant health messages and trivia factoids (ie, messages including facts and quotes from historical African American figures and trivia pertaining to African Americans, Africa, or the African diaspora) to the extant pool of SMS text messages. Altogether, these features were incorporated into the current iTAB intervention to meet the diverse needs of the target population.

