## Results

### Study Enrollment

Study enrollment began in November 2017 and closed in July 2019. A total of 90 participants from the FHCSD enrolled in the iTAB intervention. Given the timing of enrollment of the last study participant, we anticipate completing data collection in July 2020. As of April 2020, 64 participants have completed the study. Two participants have withdrawn from the study, resulting in the total sample of 88 participants.

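### The stated 74% power is for a one-sample test against a fixed 77% and is not established for the planned McNemar test

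*Protocol article*

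**What the plan says.** The Statistical Methods section sets the analysis of virologic suppression: "We will use McNemar test for paired proportions to compare virologic control within-subjects using data from the baseline and final study visits". This matches the hypothesis in the Outcomes section, which compares suppression at the end of the study with suppression at study entry in the same people.

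The next sentence gives the only power statement in the article. It opens "Based on a 2-sided, 1-sample test for proportions to compare the viral suppression rate before and after the 48-week study", continues "we have 74% power to detect an increase of 11% in suppression rate", and gives the inputs as "ie, from the reference 77% to 88%) with N=88 participants and alpha =.05".

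The 77% appears twice elsewhere. The Introduction dates it: "When this project was conceived in 2016, only 77% of African Americans receiving care at FHCSD were virologically suppressed". The Outcomes section puts the same figure in the present tense: "Currently, 77% of African Americans living with HIV receiving services at the FHCSD are virally suppressed". Both describe clinic patients, not the enrolled participants.

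The 88 comes from the Study Enrollment section: 90 enrolled less 2 withdrawn. The same section reports "As of April 2020, 64 participants have completed the study".

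**The concern.** The two tests address different null hypotheses. The one-sample test asks whether the final suppression rate differs from a constant and uses no baseline data from participants, although the sentence describes it as a before-and-after comparison. McNemar asks whether participants who gain suppression outnumber those who lose it. Its power depends on both of those proportions, not only on their difference of 11 points, and the article states neither.

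Viral suppression is a primary outcome, and the Future Directions section makes a later randomized trial depend on the findings. A non-significant McNemar result would be read against a 74% chance of detection. If a few participants lose suppression during follow-up, the real chance could be well below that. If almost none do, it could be well above.

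**Working it through.** **Inputs.** From Statistical Methods: p0 = 0.77, p1 = 0.88, n = 88, two-sided alpha = 0.05. The article gives no discordant-pair rate, so the proportion losing suppression is varied here as an assumption.

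**Step 1: reproduce the 74%.** For a one-sample z test against a fixed p0:

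power = Φ{[(p1 − p0) − 1.96·√(p0(1 − p0)/n)] / √(p1(1 − p1)/n)}

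- √(0.77 × 0.23 / 88) = 0.04486
- √(0.88 × 0.12 / 88) = 0.03464
- (0.11 − 1.96 × 0.04486) / 0.03464 = 0.637, and Φ(0.637) = 73.8%

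The exact binomial version (reject at 76 or more of 88) gives 74.6%. Other two-sided versions do not match: continuity-corrected 68.2%, arcsine 78.4%, Wald 88.8%. The published figure is therefore the one-sample test it names, correctly calculated.

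**Step 2: power of the planned test.** Let L be the proportion who are suppressed at baseline but not at the end, and G the proportion who move the other way. The margins force G = L + 0.11, so total discordance is D = 2L + 0.11. The number of discordant pairs is m ~ Binomial(88, D). Given m, the number of gains is Binomial(m, G/D). Power is the summed probability of all outcomes that reject at two-sided .05 in favour of improvement. *Exact* means the binomial test on the discordant pairs. *Asymptotic* means the uncorrected chi-square. Both are fully enumerated.

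| L (lose) | G (gain) | D | Exact | Asymptotic |
|---|---|---|---|---|
| 0% | 11% | 11% | 93% | 99% |
| 1% | 12% | 13% | 82% | 89% |
| 2% | 13% | 15% | 73% | 81% |
| 3% | 14% | 17% | 66% | 74% |
| 4% | 15% | 19% | 60% | 69% |
| 5% | 16% | 21% | 55% | 64% |
| 6% | 17% | 23% | 51% | 60% |
| 9.2% (independent visits) | 20.2% | 29.5% | 40% | 50% |

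The last row takes the two visits as independent: L = 0.77 × 0.12 = 0.0924 and G = 0.23 × 0.88 = 0.2024.

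**Step 3: where 74% holds.** Solving for L at 74% power gives 1.9% (exact) and 3.0% (asymptotic). In 88 people that is 0.019 × 88 = 1.7 and 0.030 × 88 = 2.6, or about two to three participants losing suppression.

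**Step 4: fewer complete pairs.** The N of 88 assumes that every remaining participant has a final viral load. With 75 complete pairs (an illustrative assumption, not a figure from the article) and L = 3%, McNemar power is 57% exact and 66% asymptotic.

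**The case against.** The strongest reply is that nothing is concealed and nothing is miscalculated. The sentence names its test and its reference value, the figure reproduces, and McNemar is a valid test of the paired hypothesis. Sample size, type I error and the eventual estimate are unaffected. A full range over discordance could sit in a fuller protocol. All of that is fair, but it does not answer the mismatch: two adjacent sentences present one test as the analysis and another test's power as the study's power.

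Three stronger readings are tempting, and the article does not support them.

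- **The true power is not 74%, or must be lower.** McNemar power equals 74% at about 2-3% loss, exceeds it below that and falls short above it. The article also leaves the McNemar version unnamed, and that alone moves power by 6 to 11 points in the table.
- **Participants start above 77% because all are on ART.** No section gives the enrolled baseline rate or the share on ART behind the 77%. Recruitment used several routes, including phone invitation of patients with no upcoming appointment, so the rate could lie either side of 77%. Nor would a higher start by itself reduce power: with the 11-point increase kept, one-sample power is 81% for 80% to 91% and 86% for 82% to 93%.
- **The 64 completers by April 2020 show that final viral loads will be missing.** Collection was open until July 2020, and viral loads come from clinic records or from the participant, so a late or missed study visit does not mean a missing value.

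**Conclusion.** The point stands as a mismatch between the planned test and the test used for power: the 74% is not established for the McNemar comparison. For the article's own margins, N and alpha, power ranges from 93% / 99% (exact / asymptotic) with no losses to 40% / 50% with independent visits. It drops below 74% once more than about 1.9% (exact) or 3.0% (asymptotic) of participants lose suppression. At 5% loss the shortfall is 74 − 55 = 19 points exact or 74 − 64 = 10 points asymptotic. These figures rest on the stated 77% and 88% and on assumed loss rates. Without a loss rate, the document fixes neither the size nor the direction of the error.

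Two smaller points also hold: N = 88 allows for no missing final viral loads, and the present-tense description of the 77% in Outcomes conflicts with the 2016 date in the Introduction. The power sentence is wrong as written and should be corrected, but the planned analysis need not change.

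**What to change.** Replace the power sentence with McNemar power for the 11-point increase (77% to 88%) that:

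- names the McNemar version to be used;
- covers a stated range of loss rates, for example 0-6% of participants;
- shows results for 88 pairs and for a smaller number of complete pairs labelled as an assumption, for example 75.

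In the Outcomes section, describe the 77% as the 2016 clinic-wide planning value.

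The cost is one paragraph and one rewording, with no extra enrolment, data or design change. The single 74% becomes a range that may look less favourable.

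### The stated 74% power belongs to a one-sample test against a fixed 77%, not to the planned McNemar test, whose power depends on unstated gain and loss proportions

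*Protocol article*

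**What the plan says.** The Statistical Methods section names the analysis: "We will use McNemar test for paired proportions to compare virologic control within-subjects using data from the baseline and final study visits". The next sentence gives the power: "Based on a 2-sided, 1-sample test for proportions to compare the viral suppression rate before and after the 48-week study, we have 74% power". It completes the inputs with an 11-point increase ("ie, from the reference 77% to 88%) with N=88 participants and alpha =.05").

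The Outcomes section under Data Collection, Management, and Analysis frames the hypothesis as a change within the cohort, with suppression "at the end of the study period (either week 24 or 48) compared to the proportion at study entry". It gives the same target: "We hypothesize an increase of 11% (ie, from 77% to 88%) in the proportion of participants".

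The 77% is a clinic figure. The same Outcomes section says "Currently, 77% of African Americans living with HIV receiving services at the FHCSD are virally suppressed", and the Introduction dates it: "When this project was conceived in 2016, only 77% of African Americans receiving care at FHCSD were virologically suppressed".

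The article gives no expected proportion gaining suppression, no expected proportion losing it, and no within-person correlation.

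**The concern.** Two adjacent sentences describe different tests. The one-sample test compares the final suppression rate with a constant. It gives 77% no sampling error and makes no use of participants' own baseline values, although the sentence presents it as a before-and-after comparison. McNemar's test uses only the discordant participants: those who go from unsuppressed to suppressed, and those who go the other way. Marginal rates of 77% and 88% fix the difference between these two groups but not their sizes, and power depends on the sizes.

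At stake is how the result will be read. Viral suppression is a primary outcome, and this is the only power statement in the article. A non-significant McNemar result would be interpreted as coming from a test with 74% power, when the actual power could be clearly lower or higher. The Future Directions section makes a randomized trial conditional on this study's findings, so that reading matters.

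**Working it through.** **Inputs from the article.** N = 88; reference rate 0.77; target rate 0.88; difference d = 0.11; two-sided alpha .05 (z = 1.96).

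**Step 1: reproduce the stated figure.** One-sample z test, with the null standard error for the critical value and the alternative standard error for power:

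- Null SE = √(0.77 × 0.23 / 88) = 0.04486; critical distance = 1.96 × 0.04486 = 0.0879.
- Alternative SE = √(0.88 × 0.12 / 88) = 0.03464.
- Power = Φ[(0.11 − 0.0879) / 0.03464] = Φ(0.637) = 73.8%.

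The exact binomial version (reject at 76 or more of 88) gives 74.6%. The stated 74% is therefore correct for the test it names.

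**Step 2: what McNemar needs.** Let c be the share of all participants who lose suppression and b = c + 0.11 the share who gain it. The discordant share is ψ = b + c = 0.11 + 2c. The article does not give c, so it is an assumption here. The marginal rates allow c from 0 to 0.12. If baseline and final status were independent, c = 0.77 × 0.12 = 0.0924. Larger values need negative within-person correlation.

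**Step 3: power of McNemar's test at N = 88.** The normal approximation is Φ[(d√N − 1.96√ψ) / √(ψ − d²)]. For example, at c = 0.05, ψ = 0.21 and power = Φ[(0.11 × 9.381 − 1.96 × 0.4583) / √(0.21 − 0.0121)] = Φ(0.30) = 62%. The approximation is poor when few discordant pairs are expected, so the exact, mid-p and uncorrected tests were also evaluated by summing over all possible discordant counts.

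| Lose suppression (assumed) | Gain suppression | Expected losses of 88 | Exact | Mid-p | Uncorrected | Normal approx. |
|---|---|---|---|---|---|---|
| 0% | 11% | 0 | 93% | 97% | 99% | 89% |
| 1% | 12% | 0.9 | 82% | 89% | 89% | 83% |
| 2.5% | 13.5% | 2.2 | 69% | 77% | 77% | 74% |
| 5% | 16% | 4.4 | 55% | 63% | 64% | 62% |
| 9.24% (independence) | 20.24% | 8.1 | 40% | 46% | 50% | 48% |

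**Step 4: where 74% holds.** Power equals 74% at a loss of about 1.9% for the exact test (0.019 × 88 = 1.7 participants), 2.5% by the normal approximation (2.2 participants), and 3% for the uncorrected and mid-p tests (2.6 participants). In every version this is roughly 2 of 88, at most between 2 and 3.

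**The case against.** The best defence is that nothing is miscalculated or hidden. The power sentence names its test openly and calls 77% the reference, and the figure reproduces. This stands: the fault is a mismatch between power method and analysis, not an arithmetic error.

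A second defence is that McNemar's test suits the stated hypothesis whatever its power. Enrolment had closed with 90 participants, so N could not be raised, and the stated power was already below 80%. This also stands, and it limits the severity. The correction changes no estimate, P value or type I error rate.

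A reader might go further and infer that true power may be as low as 41%, or that it is in effect a coin flip. The article does not support either. The 41% is the normal approximation at 12% loss, where nobody unsuppressed at baseline stays unsuppressed; that implies a within-person correlation of about −0.20. It is a mathematical bound rather than a planning scenario. Power near 50% needs about 9% loss with the uncorrected test, where baseline status says almost nothing about final status, or about 6% with the exact test. The article gives no loss rate, so neither a high nor a low value can be asserted.

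Nor is 74% necessarily too high. With loss below about 2%, McNemar power exceeds 74% in every version. Capping the range at 89% would also be wrong, because that value is the normal approximation where it fails; enumeration gives 93–99% at zero loss.

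None of this rescues a single figure of 74% as the power of the planned test.

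**Conclusion.** The concern holds as a mismatch: 74% is correct for a one-sample test against a fixed 77% but is not a property of the planned McNemar analysis. Without negative within-person correlation, power at N=88 lies between about 40–50% (9.2% loss) and 93–99% (no loss), depending on the McNemar version and the unstated loss proportion. The stated figure applies only if roughly 2 of 88 participants lose suppression.

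This rests on the article's marginal rates of 77% and 88%, with 77% taken as the participants' own baseline although it is a 2016 clinic-wide rate. It also assumes a paired viral load for all 88. Missing pairs would lower power: with an assumed 80 pairs and 5% loss, it is 50% (exact) to 60% (uncorrected).

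This should be fixed, because the only power statement misdescribes the planned test. It is not critical, because the McNemar test remains valid.

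**What to change.** Replace the one-sample sentence with power for the planned McNemar test at N=88. Name the version (exact, mid-p or uncorrected), state the assumed gain and loss proportions, and show power over a short range of loss, for example 1%, 2.5%, 5% and 9%. Any remark about where 74% applies should be tied to the named version. If a comparison with a fixed 77% was intended, name the one-sample test as the analysis instead, and stop describing it as a before-and-after comparison.

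The cost is one rewritten sentence and a small table, with no further enrolment. A single figure becomes a range, less favourable wherever the assumed loss exceeds about 2–3%.

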#### Outcomes

Undetectable plasma viral load and ART adherence (as measured by participants’ responses to daily SMS text messages) are the primary outcomes for this single-arm trial. In addition, participants complete an in-person comprehensive battery of psychosocial assessments at the baseline, interim, and end-of-study visits (at either Week 24 or Week 48). Specific assessments administered at each study visit are listed in Table 3. Assessments with strong reliability and validity among HIV populations were chosen, where possible. Measures collected at the baseline study visit include plasma viral load (abstracted from FHCSD electronic medical records), medication adherence behaviors (eg, percentage of adherence in the past 30 days), psychosocial risk factors associated with poor HIV-related outcomes among PWH (eg, sociodemographic characteristics, substance use, and social support), and culturally specific risks for nonadherence among African Americans (eg, subjective experiences of discrimination, HIV-related stigma, and medical mistrust). Measures collected at interim study visits (ie, every 12 weeks) are a subset of the baseline measures (eg, perceived stress, alcohol use, substance use, and depressive symptoms). Upon completion of the intervention (at either week 24 or 48), participants complete a subset of psychosocial assessments, as well as a feedback questionnaire assessing their experience, satisfaction with, and perceived usefulness of the intervention. Laboratory data on HIV-disease characteristics (eg, plasma viral load and CD4 count) and utilization of FHCSD services are collected from electronic medical records by care coordinators at each in-person study visit.

**Table 3 table3:** Assessments administered^a^

Domain		Assessments	Baseline	Week 12, 36	Week 24, 48

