**Factors that may impact antiretroviral therapy adherence**					
	Sociodemographic characteristics	Self-reported sex, gender, age, race, ethnicity, birth location, relationship status, HIV status disclosure, employment, income, housing stability, education	X		
	Depression symptoms	Beck Depression Inventory-II (BDI)	X	X	X
	Alcohol and illicit substance use	Alcohol Use Disorders Identification Test (AUDIT) and Drug Abuse Screening Test (DAST-10 Modified)	X	X	X
	Subjective social status	MacArthur Scale of Social Status Scale	X		
	Beliefs related to HIV medications	Beliefs Related to Medications Questionnaire	X		
	Supports and barriers to adherence	Supports and barriers to adherence	X		
	Self-efficacy for medications	Self-efficacy for managing medications and treatments	X	X	X
	Illicit substance use and sexual behaviors	Risk Questionnaire	X		X
	Collective self-esteem	Collective Self Esteem Scale	X		X
	Medical mistrust	Trust in the medical system; attitudes toward the health care	X		X
	Instrumental and social support	NIH Toolbox Emotional Support, Instrumental Support, and Loneliness scales	X		X
	Beliefs about HIV	Beliefs about HIV	X		X
	Subjective experiences of discrimination	Everyday Discrimination Scale; Multiple Discrimination Scale	X		X
	Quality of life	Medical Outcomes Study: 36-item Short Form Survey (MOS: SF-36)	X	X	X
	Personality	Ten-Item Personality Inventory	X		
	Perceptions of stress	Perceived Stress Scale	X	X	X
	Lifetime exposure to stress/adversity	Negative life events	X		
	Health care utilization	Utilization of care	X		X
	Health literacy	Short Assessment of Health Literacy-English (SAHL-E)	X		
	Stigma and psychosocial aspects of living with HIV	HIV Stigma Scale	X		
	Religiousness/Spirituality	Brief Multidimensional Measure of Religiousness and Spirituality	X		
	Cellphone Usage	Cellphone Usage Questionnaire	X		
	Medication-taking behavior^e^	Medication-Taking and Text-Responding Behavior Questionnaire			X
	Intervention feedback^e^	iC-CHANGE Feedback Questionnaire (Likert scales of feasibility, acceptability, and satisfaction)			X

^a^The X denotes those visits where the assessment will be administered.

^b^Data collected from electronic medical records from FHCSD clinical visit during the study period or provided by the participant.

^c^FHCSD: Family Health Centers of San Diego.

^d^ART: antiretroviral therapy.

^e^Administered only at the final visit.

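### The planned conditional logistic regression cannot estimate the demographic associations it is named for, because those factors do not vary within participant

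*Protocol article*

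**What the plan says.** All of the following is in the protocol article.

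- **Model and target** (Statistical Methods, secondary/sensitivity analyses): "multivariable conditional logistic regression analysis will be performed to study the association between demographic factors and plasma viral load". The same sentence also gives the adjustment set: "adjusting for baseline demographic variables and clinical characteristics". A P<.10 rule then brings in further covariates: "Variables with some association to plasma viral load".
- **Pairing** (same section): the primary comparison is the "McNemar test for paired proportions to compare virologic control within-subjects using data from the baseline and final study visits". No other matching is described.
- **Design** (Outcomes, under Participants, Interventions, and Outcomes): viral load and text-reported adherence "are the primary outcomes for this single-arm trial". There are no matched controls.
- **Outcome** (Outcomes, before Statistical Methods): suppression is binary. The hypothesis is that "a greater proportion of iTAB participants will be virologically suppressed (viral load <40 copies/mL) at the end of the study period" than at entry.
- **Demographic factors** (Table 3): "Self-reported sex, gender, age, race, ethnicity, birth location, relationship status, HIV status disclosure, employment, income, housing stability, education". This row is marked at baseline only, so each participant has one value per item.

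**The concern.** Conditional logistic regression compares observations inside a matched set and removes everything the set has in common. If the set is the participant, what is removed includes sex, race, birthplace, education and every other item recorded once at entry. Those items are the exposures the sentence wants to study. The model named and the question named are therefore incompatible.

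The question at stake is which participants are, or become, suppressed. With this model the analyst would get no estimate for the demographic terms, and would have to choose another model or another question after seeing the data. Prespecification is meant to prevent that.

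**Working it through.** **1. The plan's own figure.** No figure is given for the conditional model. The nearby power statement is a 2-sided 1-sample test, 77% versus 88%, N=88, alpha .05. Using the null variance for the critical value and the alternative variance for power:

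- Null SE = sqrt(.77 × .23 / 88) = .0449; alternative SE = sqrt(.88 × .12 / 88) = .0346.
- Power = Phi((.11 − 1.96 × .0449) / .0346) = Phi(.637) = 73.8%.

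The stated 74% reproduces and is not in dispute.

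**2. The conditional likelihood.** Let a participant have covariates x1 at baseline and x2 at the final visit, with coefficient vector b. A participant with the same status at both visits contributes nothing. A participant suppressed at exactly one visit, say visit s, contributes

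exp(b'x_s) / [exp(b'x1) + exp(b'x2)].

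If x1 = x2, this equals 1/2 for every value of b. The data carry no information on b, whatever the sample size. This applies to each demographic factor in Table 3 and to each baseline-fixed adjuster.

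**3. Numerical check.** Data were simulated for 88 participants with two visits each, with true non-zero age and sex effects built in. In that data set 28 participants were discordant.

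- The conditional log-likelihood was −19.408 for sex coefficients of −2, −0.5, 0, 0.5 and 2, and also for age coefficients from −0.2 to 0.2. This is 28 × ln(1/2) = −19.408, as step 2 predicts.
- Fits with age and sex as main effects, with or without a visit term, had a non-invertible Hessian and gave no standard errors.
- A visit-only model could be fitted (coefficient 0.29, SE 0.38). So could a model with visit and visit-by-age (interaction 0.47 per 10 years, SE 0.38).

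**4. How many participants would inform the estimable terms.** The documents give no discordance figure, so a range is needed. With 77% suppressed at baseline and 88% at the end, gains minus losses = .11. Losses cannot exceed the 12% unsuppressed at the end.

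| Share losing suppression | Share gaining | Discordant share | Of 88 |
|---|---|---|---|
| 0 | .11 | .11 | 9.7 |
| .03 | .14 | .17 | 15.0 |
| .06 | .17 | .23 | 20.2 |
| .12 (maximum) | .23 | .35 | 30.8 |

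About 10 to 31 participants would contribute, and about 57 to 78 would not.

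**5. Events available to an alternative model.** Unsuppressed participants number 88 × .12 = 10.6 at the end and 88 × .23 = 20.2 at the reference rate, so about 11 to 20.

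**The case against.** **The strata and terms are not stated, and an article may leave them to the analysis plan.** This is true of the detail. But the article does name the model, its target and its adjustment set, and a single-arm study without matching offers no stratum other than the participant. If ordinary logistic regression was meant, the wrong model is named and the sentence still needs correcting.

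**Conditional logistic regression is the natural regression extension of McNemar's test.** This stands. With visit and visit-by-covariate terms it can show whether demographic factors relate to change in suppression. A reader might infer that the model returns nothing at all, and that goes too far. What fails is the main effects and the baseline adjustment, which is what the sentence asks for. Clinical measures that Table 3 repeats, such as CD4 count, could also enter if their visit values were used, but that would not rescue the demographic terms.

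**Other models are planned.** Statistical Methods goes on to list linear mixed or multilevel models, growth models and regression-based models. They are generic and carry no demographic aim, and the mixed model named is linear although suppression is binary. They show that suitable tools are at hand, but they do not repair the named analysis.

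**Dropping unchanged participants is not a separate fault.** McNemar's test does the same. It matters here only because it limits the precision of any interaction.

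**The P<.10 rule.** A reader might infer that this screening will produce false predictors. The documents do not support that. They do not state how many candidates will be screened (Table 3 lists 12 sociodemographic items and the clinical ones are not counted), and screened variables enter as covariates for adjustment. As an illustration only, testing 20 independent null variables at .05 with no screening would already give 1 − .95^20 = 64% with at least one false positive. No inflation can be laid at the rule itself.

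**Conclusion.** The point holds for the demographic main effects and the baseline-fixed adjusters. They are not estimable in the named model at any sample size. This rests on two readings of the article: the matched set is the participant, and the demographic factors enter with the single value collected at baseline. Adding the Week 24 viral load of 48-week participants would enlarge some sets but would not change the cancellation.

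The visit effect and visit-by-covariate interactions remain estimable but are not planned. They would rest on about 10 to 31 of 88 participants if the planning rates hold, enough for very few and imprecise terms.

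The consequence is limited to an analysis labelled secondary/sensitivity. The McNemar comparison, the power statement and the conduct of the trial are untouched.

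**What to change.** Change the sentence in Statistical Methods so that model and target agree. Any one of these would do:

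- **Logistic regression of final-visit suppression** on the demographic factors, adjusting for baseline suppression, with a penalised (Firth) likelihood if events are sparse. This asks who is suppressed at the end, given where they started.
- **A GEE or mixed-effects logistic model over both visits**, with a visit term. Demographic main effects are then estimable, and visit-by-covariate terms can be added if change is of interest.
- **Keep conditional logistic regression and restate its target** as visit-by-demographic interactions, limited to very few terms named in advance.

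The cost is analysis wording only; no new data are needed. The downside is that few covariates can be supported: about 11 to 20 unsuppressed participants are expected for the first two options, and about 10 to 31 discordant participants for the third.
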